## Abstract

The prevalence of obesity with comorbid binge eating behaviour is growing at a faster rate than that seen for either obesity or eating disorders as separate conditions. Approximately 6% of the population are affected and they potentially face a lifetime of poor physical and mental health outcomes and an inability to sustain long-term weight loss. Current treatment options are inadequate in that they typically address either obesity or eating disorders exclusively, not the combination of both conditions. By treating one condition without treating the other, relapse is common, and patients are often left disappointed with their lack of weight loss. An integrated approach to treating these individuals is needed to prevent a worsening of the comorbidities associated with excess body weight and eating disorders. A new therapy has recently been developed, named HAPIFED, which addresses both overweight/obesity and comorbid binge eating behaviour with the combination of behavioural weight loss therapy and cognitive behaviour therapy-enhanced (CBT-E). The aim of this paper is to document the protocol for the Real Happy Study, which will evaluate the effectiveness of the HAPIFED program in treating overweight or obesity with comorbid binge-eating behaviour in a real-world setting.

## 1. Background

The prevalence of obesity with comorbid eating disorder behaviours such as binge eating is high and rapidly rising [1]. Data from large, cross-sectional, representative community samples of adults from South Australia, established that in 2015, almost 6% of the population had obesity with binge eating behaviours, an increase of 7.3-fold over the previous 20-year period. This represents a faster rate of growth in prevalence than that seen for either obesity or binge eating behaviour as separate conditions, with respective increases of 2-fold and 5.3-fold over the same time period [1]. This significant population-wide growth is consistent with the prevalence of binge eating reported in individuals with overweight or obesity as described in a number of international publications [2,3]. For instance, a review of 30 studies of individuals with overweight or obesity reported that between 16% and 51.6% engaged in binge eating behaviour [2]. A higher prevalence was reported in a large sample of 45,477 US military veterans with overweight or obesity and seeking assistance for weight management, whereby 78% of participants self-reported binge eating with associated feelings of loss of control, at least twice a week [3].

Eating disorders are defined in the American Psychiatric Association’s Diagnostic and Statistical Manual of Mental Disorders—5th Edition (DSM-5) and include a range of conditions, such as anorexia nervosa, bulimia nervosa, binge eating disorder, as well as other specified and unspecified feeding and eating disorders (OSFED and UFED). The DSM-5 defines both binge eating disorder and bulimia nervosa as consisting of recurrent episodes of binge eating, characterised by the consumption of an objectively large amount of food during a discrete period of time, such as 2 h. In addition, individuals must experience a sense of loss of control over eating during such episodes, with feelings of being unable to stop eating or control what or how much is being consumed. To meet the DSM-5 criteria, the binge eating behaviour must occur on average at least once a week for a period of three months. Binge eating disorder is further defined by the DSM-5 as causing significant distress and including three or more of the following criteria: eating much more rapidly than normal; eating until feeling uncomfortably full; eating large amounts of food when not feeling physically hungry; eating alone because of feeling embarrassed by how much is being eaten; feeling disgusted with oneself, depressed or very guilty afterward. Bulimia nervosa differs from binge eating disorder in that it is characterised by the presence of recurrent compensatory behaviour in an attempt to prevent weight gain as a result of binge eating. Such behaviour includes self-induced vomiting, misuse of laxatives, diuretics or other medication, fasting, and excessive exercising. Individuals with bulimia nervosa also judge their self-worth to a large degree in terms of their body weight and shape and their ability to control them. As mentioned above, the DSM-5 also lists OSFED as an additional eating disorder diagnosis for feeding or eating behaviours. OSFED is used to define conditions that do not meet the full criteria for any of the specified eating disorder diagnoses, but still cause significant distress to the individual. For example, binge eating disorder of low frequency and/or limited duration would apply to a situation where all of the criteria for binge eating disorder are met, however, at a lower frequency than once a week and/or for less than three months’ duration [4].

There is a growing body of evidence demonstrating that obesity with concurrent eating disorder behaviours is associated with poorer health outcomes than for obesity or eating disorder behaviours individually. In addition to the usual comorbidities that frequently occur with obesity, such as heart disease, stroke, and diabetes [5], a higher prevalence of mood, anxiety, and personality disorders are reported in individuals with obesity and comorbid binge eating [6]. Additionally, higher body mass indices (BMIs) and poorer weight loss outcomes have been reported in treatment-seeking individuals with obesity and binge eating disorder, compared to their counterparts presenting for the same obesity treatment but without a binge eating disorder [7,8].

Despite the apparently greater health needs of individuals with obesity and comorbid binge eating disorders, they are not receiving adequate treatment. Current treatments typically address either obesity or binge eating disorders exclusively, and not the combination of both conditions. Individuals with obesity and comorbid binge eating disorders want and seek to lose weight [9], and generally present for weight loss interventions rather than for treatment of their eating disorder [10,11]. Whilst a number of weight loss interventions may initially be successful in assisting individuals to lose weight [8], weight loss outcomes have been reported to be 50% less in the presence of comorbid binge eating compared to individuals receiving the same treatment and not engaging in binge eating behaviour [12]. This is because the psychopathology that maintains an individual’s tendency to binge is usually not addressed in weight loss interventions [13], meaning that relapses in binge eating behaviour and subsequent weight regain are likely [14,15,16]. 

Although reductions in binge eating behaviour have been demonstrated with behavioural weight loss therapy [17,18], previous research has shown that adjunctive cognitive behaviour therapy (CBT) results in a significantly greater reduction in binge eating than that seen with behavioural weight loss therapy alone [18]. Cognitive behaviour therapy-enhanced (CBT-E) is an alternate form of CBT, differing in that it is designed specifically to treat eating disorders. It is an effective, evidence-based, transdiagnostic treatment [19,20,21] with a core component that addresses the psychopathology that maintains an individual’s eating disorder such as the overvaluation of weight and shape. CBT-E is considered the ‘gold standard’ therapy; however, it does not encourage weight reduction [22,23]. A clinical trial and observations from a clinical setting have shown that when individuals engage in such treatment for their eating disorder behaviours, they are typically not satisfied with the treatment due to their lack of weight loss [9,24].

Weight reduction has historically not been addressed in individuals receiving treatment for their eating disorders, due to a concern that it may exacerbate binge eating or other eating disorder behaviours [25,26]. Recent reviews, however, have shown that clinically supervised dietary obesity treatments do not trigger or worsen binge eating behaviour, albeit most studies have been of short duration (less than 12 months) [27]. A further consideration in treating individuals with binge eating is that by treating only the eating disorder and not addressing the excess body weight, the health implications associated with obesity remain.

While the health consequences of obesity are numerous and well documented [28,29,30,31,32,33], overweight is also associated with a number of adverse health outcomes [34,35,36]. For example, a recent study looking at the relationship between BMI and onset of type 2 diabetes mellitus in individuals aged over 65 years, showed that men and women with a BMI in the overweight range (25–29.9 kg/m^2^) were at a 30% and 10% greater risk, respectively, of developing type 2 diabetes mellitus, compared to individuals with a BMI in the healthy weight range (<25 kg/m^2^) [36]. With losses of 5–10% of body weight, reductions in the incidence of type 2 diabetes mellitus are seen [37,38]. Greater reductions in body weight (i.e., 15 or 20%) have been shown to yield greater improvements in health outcomes, illustrating that the health benefits of weight loss are dose-dependent [39,40,41,42]. Besides reductions in the risk of type 2 diabetes, other health benefits associated with weight loss include improvements in risk factors for cardiovascular disease [38], better sleep [43,44], improved fertility and pregnancy outcomes [45,46], as well as less pain associated with osteoarthritis [47,48,49,50,51]. Improvements in psychological well-being [43,52,53] and quality of life [53,54,55] have also been shown to occur. Therefore, by not addressing excess body weight in the treatment of individuals with overweight or obesity and comorbid binge eating behaviour, such individuals are being denied the physical and mental health benefits that generally accompany weight loss. 

Given the lack of comprehensive treatment options available for individuals with overweight or obesity and comorbid binge eating, there is a high risk that such individuals may ‘slip through the cracks,’ with their ongoing binge eating potentially contributing to further weight gain and a worsening of the comorbidities associated with excess weight and eating disorders. Therefore, there is a need for therapies that take an integrated approach by addressing both the overweight or obesity and eating disorder components. 

A new program, entitled HAPIFED (A **H**ealthy **AP**proach to we**I**ght management and **F**ood in **E**ating **D**isorders) has recently been developed which aims to bridge the gaps in currently available therapies by combining both behavioural weight loss therapy to address overweight or obesity with CBT-E, to treat the eating disorder psychopathology [56]. However, since this is a new and novel program, evaluation is required.

A randomised controlled trial comparing the HAPIFED program with CBT-E, which—as mentioned above—has no weight loss component, is currently underway in Brazil [57]. To complement the findings from that randomised controlled trial and to develop strategies to enhance translation of the HAPIFED program into wider-scale clinical practice, we have chosen to measure effectiveness in a real-world setting. The eligibility criteria for real-world studies are less rigid than those for randomised controlled trials, allowing for a study population that is more representative of the population at large. This enables the external validity of results to be established, making them more applicable and generalizable to clinical practice [58]. Moreover, because the implementation of an intervention in a real-world study is more flexible than in a randomised controlled trial, the HAPIFED program may be modified to suit a real-world setting, with these modifications noted and used to further enhance the program for clinical practice [58]. As such, the information derived from the real-world assessment of the HAPIFED program will be complementary to that derived from the randomised controlled trial and provide further insight into how individuals with eating disorders might best be treated with this new program.

The aim of this paper is thus to outline the protocol for the Real Happy Study: a real-world assessment of the HAPIFED program. 

## 2. Methods

### 2.1. Clinical Hypothesis

We hypothesize that the HAPIFED program for the treatment of individuals with overweight or obesity and comorbid binge eating behaviours will result in weight loss and a reduction in binge eating and eating disorder symptoms, as assessed with the global score on the eating disorder examination questionnaire (EDE-Q).

### 2.2. Study Design

This will be a prospective study of the real-world effectiveness of the HAPIFED program for the treatment of individuals with overweight or obesity and who identify as having comorbid disordered binge eating behaviours that are characteristic of comorbid binge eating disorder, bulimia nervosa, or OSFED with recurrent binge eating.

### 2.3. Program

The HAPIFED program combines behavioural weight loss therapy to address overweight or obesity, with CBT-E to treat the eating disorder psychopathology. The program is designed to be led by a psychologist or therapist and conducted in groups of up to 12 individuals. It is comprised of up to 30 sessions, conducted on a weekly basis over a 6-month period. Each session is expected to last for approximately 90 min. Since this study is evaluating the real-world effectiveness of HAPIFED, the implementation of the program is at the therapist’s discretion and may be shortened or adapted in other ways to suit the individual circumstances of the therapist, participants, facilities or environments in which it is being conducted. Any deviations to the prescribed program will be captured in the evaluation of the interventions, as described in Section 2.9
*(Process Evaluation)*. 

HAPIFED focuses heavily on the self-monitoring of eating behaviour. For instance, it requires participants to record the timing of eating or drinking anything containing energy (kilojoules or kilocalories), and the emotional, psychological, social, or environmental circumstances that influence their consumption. Appetite awareness is monitored by ratings for hunger and satisfaction, which are intended to be recorded before and after each time a participant consumes anything containing energy. The recorded variables and their management are all addressed throughout the course of the program. 

The HAPIFED program is implemented in 3 stages, an overview of which is detailed below as an excerpt from the published manual. Full details of the HAPIFED program and manual are published elsewhere [56] (HAPIFED: A **H**ealthy **AP**proach to we**I**ght management and **F**ood in **E**ating **D**isorders 30 Group Session Program Manual © [name], [name], [name], [name], [name], [name], [name] 2017). 

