### 2.7. Study Procedures and Data Collection

#### 2.7.1. Screening/Baseline

Potential participants will be informed of the study by the HAPIFED therapist and provided with a copy of the study brochure listing the selection criteria and instructions on how to take part in the study and complete the online questionnaires. Interested participants will be directed to a secure online webpage that contains the ‘Information for Participants,’ an online screening questionnaire, and a consent form.

Following consent, participants will complete the online baseline questionnaires. There will be no time limit for completion of the online questionnaires; however, it is expected to take approximately 40 min and will include the following components: Height;Weight;Demographic Questionnaire: gender, marital status, ethnicity, occupation, education;Commonwealth Scientific and Industrial Research Organisation (CSIRO) Healthy Diet Score Survey [63];Eating Disorder Examination Questionnaire (EDE-Q) [64,65];Depression, Anxiety, and Stress Scale with 21 Items (DASS-21) [66];Short-Form Health Survey with 12 Items, Version 2 (SF-12v2) [67];Cost-Effectiveness questionnaire, which includes information about medication use (current medication including name of drug, total daily dose, dosing frequency, and indication).

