### 2.10. Sample Size

Based on the Australian government’s recommendation for obesity treatments that at least 50% of participants in a treatment group must achieve a weight loss of at least 5% of initial body weight to demonstrate a clinically significant benefit [69], and the HAPIFED pilot results where 50% of the sample had an EDE-Q score of less than one standard deviation (1.25) above the community normative score of 1.52 (i.e., below 2.77) [56,60] at the end of treatment (whereas all had a score above 2.77 before treatment), we estimated that a sample size of at least 164 participants (with 5% significance level and power of 80%) is required. To allow for an up to 50% attrition rate as that found in the pilot study [56], we inflated the sample size to 246 to ensure complete data. 

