### 2.11. Statistical Analysis

Paired t-tests will be used to compare continuous baseline data with follow-up data for normally distributed variables, or Wilcoxon signed-rank tests for non-normally distributed variables. McNemar’s tests will be used to analyse categorical data. Multivariable logistic regression analysis with repeated measures will be conducted to assess dichotomous outcomes (e.g., ≥5% weight loss versus not), taking into account important covariates and paired data. Statistical significance will be demonstrated with a *p*-value of 0.05 and Cohen’s d will be used to indicate effect size. Analysis will be conducted for the complete cohort (intention-to-treat), as well as for those that complete the HAPIFED program. Median number of sessions, sociodemographic factors, outcomes, and scores will be compared between completers and noncompleters. Cost-effectiveness will be assessed using the quality of life data, health service utilization costs (determined from the self-report cost-effectiveness questionnaire and costed using the Medicare Benefits Schedule), and medication costs (using the Pharmaceutical Benefits Scheme), as previously published [77,78].

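### HAPIFED is delivered in therapist-led groups, but the named before-after tests make no allowance for group or therapist clustering, so with any positive intraclass correlation uncertainty is understated

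*Protocol article*

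**What the plan says.** Section 2.3 (Program) says HAPIFED is "designed to be led by a psychologist or therapist and conducted in groups of up to 12 individuals". The same section says that "the implementation of the program is at the therapist’s discretion and may be shortened or adapted in other ways". Section 2.4 adds that the study does not itself provide the programme; therapists deliver it within their own practice. Section 2.7.1 gives the route into the study: "Potential participants will be informed of the study by the HAPIFED therapist". Participants are therefore nested in groups, and groups in therapists.

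Section 2.11 (Statistical Analysis) names the methods:

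- Continuous outcomes: "Paired t-tests will be used to compare continuous baseline data with follow-up data for normally distributed variables", with the Wilcoxon signed-rank test as the alternative.
- Categorical outcomes: "McNemar’s tests will be used to analyse categorical data".
- Dichotomous outcomes: "Multivariable logistic regression analysis with repeated measures will be conducted to assess dichotomous outcomes", and this model is described as "taking into account important covariates and paired data".

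Section 2.10 (Sample Size) states: "we estimated that a sample size of at least 164 participants (with 5% significance level and power of 80%) is required". The figure is raised to 246 for attrition. The section mentions no design effect, ICC or number of groups.

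**The concern.** Members of one group share a therapist, peers, up to 30 sessions, and whatever local version of the programme that therapist chose to run. Their outcomes are likely to be more alike than those of people in different groups. The paired t, Wilcoxon and McNemar tests handle correlation between two measurements on the same person. They make no provision for correlation between different people.

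Pairing does not remove the problem. A stable group difference present at both baseline and follow-up cancels in the within-person difference, but a shared effect of the group or therapist on the change does not. That shared effect stays in every member's difference score.

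Section 2.2 describes a prospective study with no comparison arm, so the before-after changes and the two co-primary proportions at 52 weeks carry the conclusions. If clustering is ignored, their precision is overstated.

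**Working it through.** **The plan's own figure.** The 164 in section 2.10 cannot be reproduced. The section gives an expected rate of 50% for each co-primary outcome, 5% significance and 80% power, but no comparison value, target precision or method. It can therefore be used below only as a stated number of analysed participants.

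**Inputs.**

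- Group size *m*: the document gives only a ceiling of 12 (section 2.3). I use 12 as the upper case and 6 as a lower case (a full group after the 50% attrition allowed for in section 2.10). An intermediate case is 8: 246/12 = 20.5 full groups, and 164/20.5 = 8 per group.
- ICC: not given. Assumed 0.01, 0.05 and 0.10.
- Analysed number: 164 (section 2.10). Expected proportion: 50% (section 2.10).
- Significance: 5%, taken as two-sided because the article does not state sidedness.

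**Formulas.**

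- Design effect DE = 1 + (m − 1) × ICC
- Standard error multiplier = √DE
- True size of a nominal 5% test = 2 × [1 − Φ(1.96/√DE)]
- Effective number = 164/DE
- 95% half-width for a proportion of 50% = 1.96 × √(0.25 × DE/164)

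**Worked case, m = 6, ICC = 0.05.** DE = 1 + 5 × 0.05 = 1.25. √1.25 = 1.118. 1.96/1.118 = 1.753, so the size is about 8.0%. 164/1.25 = 131. Half-width = 1.96 × √(0.25 × 1.25/164) = 8.6 points, against 1.96 × √(0.25/164) = 7.7 points under independence.

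| m | ICC | DE | SE multiplier | True size | 164 acts as | Half-width at 50% (points) |
|---|---|---|---|---|---|---|
| any | 0 | 1.00 | 1.00 | 5.0% | 164 | 7.7 |
| 6 | 0.01 | 1.05 | 1.02 | 5.6% | 156 | 7.8 |
| 6 | 0.05 | 1.25 | 1.12 | 8.0% | 131 | 8.6 |
| 6 | 0.10 | 1.50 | 1.22 | 10.95% | 109 | 9.4 |
| 8 | 0.01 | 1.07 | 1.03 | 5.8% | 153 | 7.9 |
| 8 | 0.05 | 1.35 | 1.16 | 9.2% | 121 | 8.9 |
| 8 | 0.10 | 1.70 | 1.30 | 13.3% | 96 | 10.0 |
| 12 | 0.01 | 1.11 | 1.05 | 6.3% | 148 | 8.1 |
| 12 | 0.05 | 1.55 | 1.24 | 11.5% | 106 | 9.5 |
| 12 | 0.10 | 2.10 | 1.45 | 17.6% | 78 | 11.1 |

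**Which column applies where.** The true-size column is for the before-after tests, chiefly on the continuous secondary outcomes. It does not apply to the co-primary proportions. No null value is stated for them, and both are 0% at baseline by construction: nobody has yet lost 5% of baseline weight, and section 2.6.1 admits only people with an EDE-Q global score above 2.77. For the co-primaries, the half-width column shows the consequence.

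**The case against.** The strongest case on the other side has five parts.

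1. *The article is condensed.* The covariates in the logistic model are not listed, and therapist could be among them. This stands in part. A reader might infer that every planned analysis ignores clustering. The text supports that for the paired t, Wilcoxon and McNemar tests, which are named outright and have no place for a group term. For the logistic model it shows only that the correlation described is within-person. In the completer versus noncompleter comparison, which is partly within groups, even the direction of any error is uncertain.

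2. *Twelve is a ceiling.* Not every member of a therapy group need be eligible or consent, and attrition shrinks the clusters further. This stands. A reader might take the 12-per-group rows as the expected case, but the document does not support that. With 3 analysed per group (an assumption) and ICC 0.05, DE = 1 + 2 × 0.05 = 1.10 and the true size is about 6.2%. On the other hand, a therapist who runs several groups forms a cluster that may exceed 12.

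3. *The ICC is assumed.* This also stands. At zero there is no harm, and at 0.01 it is small. A reader might infer that therapist discretion proves a large ICC. It does not, because section 2.3 also allows adaptation to individual participants, and the stage 2 content is partly individualised, so some of that variation lies within groups.

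4. *What 164 assumes is unknown.* A reader might conclude that it was calculated under independence. With no method or null value given, the most that can be said is that no design effect is stated.

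5. *The type I error figures do not attach to the co-primary outcomes.* This is correct, for the reason given at the end of the working. The harm there is intervals that are too narrow.

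None of this removes the core point. The simple tests are stated methods, not details left out, and they fit group-delivered therapy poorly.

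**Conclusion.** The concern holds for the before-after tests and for the intervals around the co-primary proportions. If the named tests are followed as written, uncertainty is understated whenever the within-group or within-therapist correlation of the outcome is positive.

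The magnitude is conditional on assumptions. Over an ICC of 0.01 to 0.10, the true size of a nominal 5% before-after test runs from about 5.6% to 11% at 6 analysed per group and from 6.3% to 17.6% at the ceiling of 12. The half-width of a co-primary interval at 50% and 164 analysed grows from 7.7 points to between 7.8 and 11.1 over the same cases. Clusters below 6 give less. The conclusion rests on the sign of the ICC; its practical weight rests on an ICC and an enrolled cluster size that the article does not report. It should be corrected, but it does not invalidate the study.

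**What to change.** 1. Record a therapist identifier and a group identifier for each participant.
2. In section 2.11, replace the simple paired tests with models of change that use cluster-robust (GEE) standard errors with a small-sample correction, or a random intercept, at group or therapist level.
3. Add the same allowance to the repeated-measures logistic model and say so in the text.
4. Report cluster-adjusted confidence intervals for both co-primary proportions.
5. In section 2.10, say that 164 includes no stated design effect and give the effective number over a range of ICCs, as in the table above.

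The cost is two data fields, a change to the analysis text and somewhat wider intervals. The number of therapists is not given, and 246/12 implies only about 21 groups if all were full. A random effect for group nested in therapist may be unstable with few therapists. In that case, clustering at the highest level with a small-sample correction is enough. No clinical procedure changes.
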